#### Other outcomes

##### Economic outcomes

We will explore whether it is feasible to link the BiBBS dataset above with other datasets that contain information on health-related outcomes and resource use.

##### Process outcomes

The process evaluation will aim to include both mothers and co-parents. The service collects information on which sessions parents attend and the number of sessions they attend, and group level information about the number of sessions delivered per programme and the deliverer for each session. Parent satisfaction questionnaires are also collected at the end of the programme. This information will be used to further explore effectiveness findings.

A process evaluation will explore parent’s experience of the course, identify the outcomes they reported after attending, and identify the barriers and facilitators to engagement of parents. The plans for this study will be specified in a separate protocol.

### Statistical methods

In addition to information provided below a detailed statistical analysis plan is in development and will be preregistered on the Open Science Framework (OSF). All analyses will be run using Stata [49].

#### Propensity score matching

A matched control group to the intervention group will be created using the propensity score matching method. The propensity score is the probability of a subject to receive a treatment conditional on the set of covariates [7]. The propensity score method with ‘one-to*-many’* matching will be applied to maximise statistical power [3], as we can utilise data from the BiBBS cohort for mothers who do not participate in Baby Steps.

Figure 1 presents a simplified Directed Acyclic Graph (DAG) created to identify confounding variables that are associated with both the treatment and the outcome [45, 52]. Figure 1 indicates the seven characteristics that we will match the groups on to estimate the effect of treatment on outcome.

**Fig. 1 Fig1:**
[figure not shown]
Directed Acyclic Graph of associations between confounders, treatment exposure, and primary outcome

Table 2 describes the covariates that we will use for propensity score matching obtained from the BiBBS baseline questionnaire completed before the child is born. All matching variables are at the level of the mother, not the child. Variables were selected to be matched upon if they were thought to have an association with both uptake of treatment, and with the outcomes (maternal sensitivity, maternal mental health), and there was empirical evidence to suggest this was the case (see references in Table 2).

**Table 2 Tab2:** Covariates for matching obtained from BiBBS baseline questionnaire

Covariates (measurement tool if relevant)	Measurement	Justification
Prenatal attachment (Prenatal Attachment Inventory)	Continuous	[13]
Prenatal Depression (PHQ-8)	Continuous	[13]
Prenatal Anxiety (GAD-7)	Continuous	[13]
Ethnicity	Categorical	[13, 41, 51]
Socioeconomic position (financial security)	Continuous	[28, 48, 51]
Mother age	Continuous	[13, 28]
Parity (first child or not)	Continuous	[48]
Speaks English	Binary	[11, 51]

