### Objectives

The current study will examine the causal effectiveness of the Baby Steps intervention in a real-world setting, within a socioeconomically deprived and ethnically diverse area in Bradford. Baby Steps is commissioned by Better Start Bradford and delivered by Action for Children. The authors of this study are independent of the delivery or design of the service.

This study will use a matched-control comparison group. The specific aims of this study are to (1) assess whether the universally and remotely delivered Baby Steps programme is effective in improving the primary outcome of postnatal maternal sensitivity and (2) the secondary outcome of postnatal maternal mental health when compared to services as usual at 6–10 weeks postnatal. This study also aims to (3) assess whether the effects of Baby Steps on postnatal maternal sensitivity are mediated by postnatal maternal mental health.

This study has additional objectives with outcomes nested in routinely linked data, however, it will be underpowered to ascertain causal effectiveness in these outcomes. We aim to (4) assess differences in birth outcomes (delivery type, weight, gestation, feeding) and (5) assess differences in the identification and prevalence of poor perinatal mental ill health inferred through routine data linkage across the two groups. Finally, the economic analysis of this study will (6) estimate the cost of the intervention (including delivery and training to deliver Baby Steps) and (7) assess the feasibility of collecting health related resource use data for a future full economic evaluation.

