### Study setting

This study is set in Bradford, a city in Northern England with high levels of socioeconomic deprivation and a large ethnic minority population [10]. Baby Steps is currently being delivered by Action for Children through the Better Start Bradford programme. Better Start Bradford is part of network of five ‘Better Start’ programmes around the UK funded by The National Lottery Community Fund with the aim to improve the life chances of over 60,000 children living in some of the poorest parts of England. Within Bradford, the initiative is delivered in three areas: Bowling and Barkerend, Bradford Moor and Little Horton (see https://www.betterstartbradford.org.uk/).

Born in Bradford’s Better Start (BiBBS) is an interventional family cohort study, which runs in parallel to Better Start Bradford and is designed to support effectiveness evaluations of Better Start Bradford’s early life interventions [21]. BiBBS is a part of the Born in Bradford (BiB) family of studies [53]. All mothers and children in the BiBBS cohort have in-depth baseline data captured during pregnancy, and consent to routine linkage to their health and education records as well as information about intervention participation. BiBBS includes an additional questionnaire to all mothers 6–10 weeks postnatally, which serves as the primary and key secondary outcomes for Baby Steps. As a part of the consent to BiBBS, mothers agree to the information about them and their child being used to evaluate interventions, either as intervention or control participants. A significant proportion of pregnant BiBBS women report mild to severe symptoms of depression (46%), and symptoms of anxiety (30%) [22].

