#### Maternal-child sensitivity (MORS-SF)

In the absence of a minimum clinically important difference for the MORS-SF, we based our sample size calculations on 0.5 of a standard deviation in the MORS-SF [16]. A recent study of a trial delivered in Better Start Bradford indicates that the standard deviation in the MORS-SF is 4.7 [9]. We will have 80% power to detect 0.5 of this difference in the MORS-SF (± 2.35, *d* = 0.50) with 130 participants total (65:65), or if we obtain a larger control group through the BiBBS additional sweep (e.g. 140 total (56:84), 150 total (50:100), 180 total (45:135)). Historical data from Baby Steps in Bradford indicate that there is approximately a 40% attrition rate between enrolling and completing the project. To detect a difference in the MORS-SF, Baby Steps should therefore aim to enrol at least 72 participants to achieve the minimum sample size of 45 participants in the intervention group at the end of the study.

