A process and implementation evaluation is planned, and this will reveal more in depth information about how the service is implemented; which will be essential to understanding our findings [46]. We have planned to assess the feasibility of collecting information through routine data for an economic analysis, as it will not be possible in this study to collect additional economic measures to conduct a full economic evaluation. If Baby Steps is found to be causally effective in the outcomes we are collecting, a future study will need to conduct an economic evaluation to address whether the programme is cost effective.

The current study is nested within the BiBBS interventional family cohort study, which was primarily designed to examine the impact of individual, and stacked, interventions and services rather than conduct observational studies. Since 2016, BiBBS has worked in partnership with Better Start Bradford to engage the community and stakeholders, clarify the design of the interventions and monitor their implementation, harness routinely collected data, and develop toolkits and operational guides. The work from this partnership utilised innovative study designs and methods to assess process outcomes, clinical outcomes, and cost evaluations – all of which has informed design of the current study and other upcoming effectiveness studies [20]. This evaluation aims to test the causal effects of the Baby Steps programme on maternal mental health and maternal sensitivity. The study results will be submitted to a relevant journal and will be shared with the local service delivery team in Bradford, Baby Steps delivery teams more widely, and commissioners of these services.

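### The matching set omits participation in other Better Start Bradford programmes, although earlier participation is a plausible confounder and linkage consent covers such data

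*Protocol article*

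**What the plan says.** **Aim.** Under Objectives: "The current study will examine the causal effectiveness of the Baby Steps intervention in a real-world setting". The comparator for aims 1 and 2 is services as usual, for example "the secondary outcome of postnatal maternal mental health when compared to services as usual at 6–10 weeks postnatal". The article does not say which local programmes that includes.

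**Setting.** Study setting describes BiBBS as "designed to support effectiveness evaluations of Better Start Bradford’s early life interventions". The Discussion adds that it was "primarily designed to examine the impact of individual, and stacked, interventions and services rather than conduct observational studies". Study setting also says that mothers give "consent to routine linkage to their health and education records as well as information about intervention participation".

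**Groups.** Under Eligibility, comparison women must never have received Baby Steps. Neither group's criteria mention any other programme.

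**Matching.** Above Table 2: "Variables were selected to be matched upon if they were thought to have an association with both uptake of treatment, and with the outcomes". The same sentence goes on to require empirical evidence for the association. The source is fixed too: "Table 2 describes the covariates that we will use for propensity score matching obtained from the BiBBS baseline questionnaire completed before the child is born". The eight rows are prenatal attachment, depression, anxiety, ethnicity, socioeconomic position, maternal age, parity and speaking English.

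**Outcome model.** Linear regression analyses adds two covariates to group: child age in days and Better Start Bradford area.

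**The concern.** The groups are defined by one programme in a population that is offered several. Women who take up one voluntary programme may be more likely to take up another. The Discussion gives some support for a link between service contact and uptake: one reason for not running an RCT was that referrals through other local services would have had to be paused. An earlier programme may also have affected sensitivity or mood. A variable related to both uptake and outcome is what matching is meant to balance, and this one is absent.

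If Baby Steps women had used other programmes more, part of a difference in MORS-SF, PHQ-8 or GAD-7 could come from those programmes or from the readiness to engage that they mark. If comparison women had used them more, a real effect could be masked. A larger sample removes neither bias.

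The article sends several details to the statistical analysis plan, but it fixes the matching variables and the two model covariates itself. The omission is therefore a choice made in this document.

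**Working it through.** **1. The plan's own figure.** Inputs from Sample size calculations: SD 4.7, difference 2.35 (d = 2.35 / 4.7 = 0.50), two-sided 5%, 80% power, two-sample t-test. The exact calculation needs 63.8, so 64 per group. The stated 65:65 gives 80.8% power, and the 45:135 alternative gives 82.4%. The figure reproduces, and the target of 2.35 points is the yardstick below.

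**2. What the design balances.** The eligibility criteria, the eight rows of Table 2 and the two model covariates contain no term for other programmes. Three rows (prenatal attachment, PHQ-8, GAD-7) would carry any change that an earlier programme had already made to attachment or mood by baseline. They would not carry a remaining effect by another route, or anything attended after baseline.

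**3. Possible size.** Let *e* be the other programme's effect on MORS-SF in SD units and Δp the difference between the matched groups in the proportion who received it. If effects add and are the same in both groups:

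bias = *e* × Δp × 4.7 points

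The documents give neither *e* nor Δp, so both are **assumed**. Results in MORS-SF points:

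| *e* | Δp = 10% | 20% | 30% | 50% |
|---|---|---|---|---|
| 0.2 | 0.094 | 0.188 | 0.282 | 0.470 |
| 0.3 | 0.141 | 0.282 | 0.423 | 0.705 |
| 0.5 | 0.235 | 0.470 | 0.705 | 1.175 |

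As a share of the target: 0.094 / 2.35 = 4%, up to 1.175 / 2.35 = 50%. If Δp = 0 the bias is zero. If comparison women use other programmes more, the sign reverses.

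**4. Effect on the test.** At 45:135 the standard error in SD units is √(1/45 + 1/135) = 0.172. If Baby Steps had no effect, the test would be centred at (*e* × Δp) / 0.172. By normal approximation the nominal 5% test would reject in 5.2% of studies at the mildest corner (0.02 SD), 8.2% at *e* = 0.3 and Δp = 30% (0.09 SD), and 30.6% at the most severe corner (0.25 SD).

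**5. Allowance for the baseline scores.** If they absorbed half of an earlier programme's effect (again an assumption), the range would halve: 0.094 / 2 = 0.05 to 1.175 / 2 = 0.59 points.

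The formula covers only the effect of the other programme itself. Confounding through willingness to engage comes on top of it and cannot be sized from the documents.

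**The case against.** **The plan does not break its own rule.** A reader might infer that it does, because earlier participation looks related to uptake and outcome. But the rule also asks for empirical evidence, and the documents give none for this variable. No contradiction is shown.

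**The other programmes are not described.** A reader might infer that they target the same outcomes and recruit through the same midwives. The article lists none of them. The nearest support is "A recent study of a trial delivered in Better Start Bradford indicates that the standard deviation in the MORS-SF is 4.7", which shows that the scale was measured in another setting there. It does not say which programme was trialled, whom it served or when it ran. Midwife referral is described for Baby Steps only. Likewise, consent to linkage does not show that complete, dated records are already held.

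**A pragmatic comparator may include other services.** This stands for participation after enrolment. Such participation may be part of services as usual, or may follow from Baby Steps, so it is not a simple confounder. It does not answer unequal participation before baseline.

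**The baseline scores already do some of the work.** This also stands, in part, as set out in the working.

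**Detail may be left to the analysis plan.** That is fair for a descriptive table or a sensitivity analysis. It is not fair for the matching set, which this article fixes.

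**Conclusion.** The point holds as a plausible and cheaply reduced source of confounding. It is not a demonstrated bias or a contradiction in the plan. The confounder proper is participation in other Better Start Bradford interventions before baseline. It is left out of a fixed matching set in a cohort built with stacked interventions in mind.

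Direction and size are unknown. The range of about 0.09 to 1.18 MORS-SF points (4% to 50% of the target) rests wholly on assumed effects of 0.2 to 0.5 SD, assumed uptake differences of 10 to 50 percentage points after matching, additive effects and no offset from the baseline scores. The upper end needs both inputs at their extremes and is not a forecast. The documents do not support a claim that the Baby Steps estimate is in fact mixed with other programmes' effects, or that a set fraction of the target effect is at risk. The case for change is that the variable is plausible, the linkage consent covers it, and the remedy is small.

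**What to change.** 1. Add one binary variable to Table 2 and the propensity model: took part in another Better Start Bradford intervention before BiBBS baseline, yes or no, taken from linked participation data. Use the same cut-off in both groups, so that the look-back is defined alike.
2. Report, by group, participation in other Better Start Bradford interventions between baseline and the 6–10 week outcome. State whether those interventions count as part of services as usual.
3. Keep later participation out of the primary model, because it may be a consequence of Baby Steps. Label any analysis that excludes later co-participants as exploratory, since it conditions on behaviour after enrolment.

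**Cost.** One more matching variable and one descriptive table, with no new data collection if the linkage works as the consent allows. Matching becomes slightly harder, and the variable is only as good as the completeness and dating of the participation records, which should be checked first.

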### Linear regression analyses 

After matched groups have been created, linear regression analyses will be run using group assignment as the independent variable, and the primary (maternal sensitivity) and secondary outcomes (maternal mental health) as the dependent variables. In addition to group assignment, two covariates will be included in the model: child age in days will be included as a continuous covariate, and Better Start Bradford area will be included as a categorical covariate with 3 levels. Models will be run for each outcome: maternal child sensitivity (MORS-SF), maternal depression (PHQ-8), and maternal anxiety (GAD-7).

We will conduct both Intention to Treat (ITT) analyses to ascertain the effects of enrolling in the intervention [23, 27], and per protocol analyses to ascertain the effects of receiving the treatment [50]. The ITT analyses will therefore include all mothers who enrolled in the intervention after an initial home visit, and the per protocol analyses will only include ‘completers’, defined as those who take part in at least 6 sessions (including at least one postnatal session).

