### Data collection procedures

The study will include all women recruited from 1^st^ May 2022, up until the end of the delivery of the service (anticipated to be at the end of 2023).

Pregnant women complete a detailed questionnaire when recruited to BiBBS regarding their prenatal attachment, mental health, socio-demographics, family circumstances and more. Data provided from this questionnaire will enable intervention and control groups to be matched, where individual intervention participants can be matched to > 1 control group participant(s) (see statistical methods section for details).

All BiBBS mothers will complete outcome measures at 6–10 weeks after birth. The data are collected either by phone or at a physical home visit. The questionnaires include: the Patient Health Questionnaire-8 (PHQ-8), Generalised Anxiety Disorder assessment-7 (GAD-7), and the Mothers Object Relations Scale-Short Form (MORS-SF) (see below for details).

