### Sample size calculations

Sample size calculations for our primary and secondary outcomes were produced using Stata-17’s *power* command for the effectiveness outcomes. Sample size calculations were based on two sample means t-test with a two-tailed alpha of 5%.

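### The outcome model is closed at child age and area, so baseline PHQ-8, GAD-7 and prenatal attachment are used for matching but never adjusted for

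*Protocol article*

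**What the plan says.** In the section on linear regression analyses, each outcome is regressed on group after matching. The covariate list is explicit and closed: "In addition to group assignment, two covariates will be included in the model", which are child age in days and area with three levels. The same model serves MORS-SF, PHQ-8 and GAD-7.

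The baseline questionnaire, completed in pregnancy, records prenatal attachment, depression and anxiety. Table 2, headed "Covariates for matching obtained from BiBBS baseline questionnaire", lists the Prenatal Attachment Inventory, PHQ-8 and GAD-7 among its eight rows. The accompanying text says that variables were chosen because they were thought to relate both to uptake and to the outcomes, with empirical support. Nothing gives them a role after matching.

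On the matching ratio, the data collection section allows one-to-many sets, "where individual intervention participants can be matched to > 1 control group participant(s". On the second analysis population, "the per protocol analyses will only include" completers, defined by sessions attended. The statistical methods section announces a detailed analysis plan that adds to what the article states.

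**The concern.** Propensity score matching balances covariates approximately and on average. With 45 to 65 intervention women under the MORS-SF scenarios and eight covariates reduced to one score, some chance and residual imbalance in individual covariates is to be expected. The stated model has no term that would correct it.

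The variables left out are ones that the protocol itself names as prognostic, and two of them are the baseline of an outcome on the same scale. Omitting them leaves explainable outcome variance in the residual. This sits awkwardly with the choice of one-to-many matching, which the protocol justifies by statistical power. What is at stake is some bias from imperfect matching and a wider confidence interval than the data in hand require.

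**Working it through.** **Inputs from the protocol article.** The sample size section uses a "two sample means t-test with a two-tailed alpha of 5" per cent. For MORS-SF, "the standard deviation in the MORS-SF is 4.7", so a target of 2.35 gives d = 2.35/4.7 = 0.50; stated sizes include 65:65 and 45:135. For PHQ-8 and GAD-7, d = 0.42; stated sizes include 62:187.

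**Input not in the protocol.** The baseline–outcome correlation r is assumed to lie between 0.3 and 0.6.

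**Step 1: reproduce the stated power.** Power is P(|T| > t₀.₉₇₅), where T is noncentral t with n₁ + n₂ − 2 degrees of freedom and noncentrality d/√(1/n₁ + 1/n₂).

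- 64:64, d = 0.50: 0.50/√(2/64) = 2.828, power 80.2%. So 64 per arm suffices, close to the stated 65.
- 65:65, d = 0.50: noncentrality 2.850, power 80.8%.
- 45:135, d = 0.50: 0.50/√(1/45 + 1/135) = 2.905, power 82.4%.
- 62:187, d = 0.42: 0.42/√(1/62 + 1/187) = 2.866, power 81.5%.

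The stated sizes reproduce.

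**Step 2: add a baseline score.** Residual variance is multiplied by 1 − r², so d becomes d/√(1 − r²).

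| r | 1 − r² | Power, 62:187 (d = 0.42) | Power, 45:135 (d = 0.50) | Power, 65:65 (d = 0.50) |
|---|---|---|---|---|
| 0 | 1.00 | 81.5% | 82.4% | 80.8% |
| 0.3 | 0.91 | 84.9% | 85.7% | 84.3% |
| 0.4 | 0.84 | 87.6% | 88.3% | 87.0% |
| 0.5 | 0.75 | 90.9% | 91.6% | 90.4% |
| 0.6 | 0.64 | 94.6% | 95.1% | 94.3% |

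These sums treat the groups as independent samples, as the protocol's own calculation does, and ignore child age and area. The MORS-SF columns are upper guides, because only a proxy baseline exists. Part of the gain is a standard error that stops being too wide: in the Step 3 simulation, with close matching on a single covariate, the spread of the estimate hardly changed with adjustment (for example 0.124 SD without and 0.123 SD with it).

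**Step 3: two related points on which the protocol is silent.** These are simulations with a true effect of zero. All inputs are assumed except the 72 enrolled women.

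- *Variable matching ratio.* There are 72 intervention women, up to three controls each, a caliper of 0.2 SD, a pool of 200 to 800, a baseline gap of 0.3 to 0.9 SD and r = 0.4. An unweighted pooled contrast was biased by 0.00 to 0.11 SD, at most 0.11 × 4.7 ≈ 0.5 MORS-SF points. Set weights or adjustment for the matching variable cut this to about 0.01 SD or less.
- *Per protocol with every control kept.* If completion depends on baseline (odds ratio 1.5 to 2 per SD, r = 0.3 to 0.5), the bias is 0.05 to 0.13 SD, or about 0.2 to 0.6 MORS-SF points. It is about zero if completion does not depend on baseline, if controls of non-completers leave with them, or if the baseline score is adjusted for.
- *Constant 1:k ratio.* With an assumed within-set outcome correlation of 0.05 to 0.30, the correct standard error is about 0.97 to 0.84 times the ordinary one.

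**The case against.** The baseline scores are not uncontrolled: they are in the propensity score, so adding them to the outcome model improves efficiency and robustness and does not repair a failure to handle confounding. That stands. It also stands that MORS-SF cannot be measured before birth, so r = 0.5 or 0.6 between prenatal attachment and MORS-SF is unsupported, and that the planned sizes reach 80% power without adjustment. None of this answers the point that the covariate list is stated and closed, and not left to the analysis plan.

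A reader might go further and infer that the regression ignores the matched sets, that its standard error is wrong, and that the per-protocol analysis breaks the match. The protocol does not support this. Weights and set-clustered variance are not covariates, so a two-covariate list does not exclude them, and nowhere is the regression said to be unweighted. One-to-many matching permits a variable ratio but does not fix one; under a constant ratio the ordinary standard error tends to be conservative. The text defines completers but does not say whether controls of non-completers are kept, dropped or re-matched. A detailed analysis plan is announced, and it commonly settles such matters. The biases in Step 3 are therefore conditional, and the first can be zero.

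**Conclusion.** The point holds as a shortcoming of the stated outcome model. Variables that the protocol itself treats as prognostic are in hand and excluded from the regression, which leaves residual post-matching imbalance uncorrected and gives away precision. For PHQ-8 and GAD-7 at 62:187 the gain forgone is about 3 to 13 percentage points of power (84.9 − 81.5 = 3.4; 94.6 − 81.5 = 13.1) for an assumed r of 0.3 to 0.6. For MORS-SF at 45:135 the corresponding figures, 3.3 to 12.7 points, are an upper guide. No stated power claim fails as a result.

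Handling of matched sets and of per-protocol controls are items for the analysis plan to confirm. They are not errors shown by the protocol.

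**What to change.** Replace the two-covariate sentence in the section on linear regression so that each outcome model also includes the Table 2 matching covariates, at minimum baseline PHQ-8, GAD-7 and prenatal attachment, alongside child age and area. The cost is a few degrees of freedom and the handling of missing baseline values, for which the missing data section already plans. No new data are collected.

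The analysis plan should also confirm two things:

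- If the number of controls per woman varies, each control is weighted 1/k within its set of k controls, and the variance is clustered on matched set.
- In the per-protocol analysis, the controls of excluded women are dropped, or completers are re-matched.

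Baseline adjustment largely removes both conditional biases on the matched variables, so the covariate change matters most. Dropping or re-matching controls does not remove selection on unmeasured drivers of completion, and the report should say so.

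### The completers-only regression is presented as the effect of receiving Baby Steps, but completion is a post-enrolment filter on one group that antenatal matching cannot fully balance

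*Protocol article*

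**What the plan says.** The Linear regression analyses section plans two analyses of each outcome (MORS-SF, PHQ-8, GAD-7). The intention-to-treat (ITT) analysis is to "include all mothers who enrolled in the intervention after an initial home visit". The second consists of "per protocol analyses to ascertain the effects of receiving the treatment", restricted to completers, "defined as those who take part in at least 6 sessions (including at least one postnatal session"). The regression model is the same for both: "In addition to group assignment, two covariates will be included in the model", namely child age and Better Start Bradford area.

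The matching covariates in Table 2 are "obtained from the BiBBS baseline questionnaire completed before the child is born". Under Eligibility, controls must have a young infant, no receipt of Baby Steps, and data in the additional postnatal sweep. Nothing corresponding to attendance is asked of them. On timing, "All BiBBS mothers will complete outcome measures at 6–10 weeks after birth". The sample size section reports "approximately a 40% attrition rate between enrolling and completing the project".

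**The concern.** The stated question is what receiving the programme does. The planned contrast asks something else: whether mothers who kept attending, including after the birth, have the same mean outcome as matched mothers who were never asked to attend. These questions coincide only if, given the matching variables, completion is unrelated to the outcome.

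There is reason to doubt that. A difficult birth or new low mood could keep a mother from the postnatal contacts and also worsen her scores at 6–10 weeks. Two of the outcomes are depression and anxiety, and the Background links perinatal mental health to bonding, so the primary outcome is exposed too. Such a mother leaves the completers. A comparable control who answers the postnatal questionnaire stays in.

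If better-adjusted mothers complete, the bias favours the programme; if mothers with more difficulties persist, it runs the other way. In the first case an ineffective programme could show a significant completer result, and a real effect would be overstated.

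**Working it through.** **Inputs from the article.** Two-sided 5% t-test, 80% power; MORS-SF SD 4.7; target 0.5 SD = 2.35 points; group sizes 65:65 and 45:135 (MORS-SF) and 62:187 (PHQ-8 and GAD-7); about 40% attrition, so 60% completing.

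**Assumptions not in the article.** Groups are equal at enrolment after matching; the programme has no effect; completers are the top 60% of a latent tendency to complete; that tendency correlates r with the outcome after matching.

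**1. The plan's own figure.** For d = 2.35/4.7 = 0.50, the noncentral t gives 64 per group (128 in total). Power at 65:65 is 0.808. The stated 130 is reproduced.

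**2. Shift in the completer mean.** Shift = r × φ(z)/0.6, where z cuts off the top 60% of a standard normal. This is 0.644 × r SD. At r = 0.3 it is 0.193 SD, or 0.193 × 4.7 = 0.91 MORS-SF points.

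**3. Rejection rate with no programme effect.** The standard error is √(1/n₁ + 1/n₂) SD, and the noncentrality is shift/SE. For 45:135 at r = 0.3: SE = √(1/45 + 1/135) = 0.172; 0.193/0.172 = 1.12; rejection 20.0%.

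| r | Shift (SD) | MORS-SF points | 65:65 | 45:135 | 62:187 |
|---|---|---|---|---|---|
| 0 | 0 | 0 | 5.0% | 5.0% | 5.0% |
| 0.1 | 0.06 | 0.30 | 6.5% | 6.6% | 7.2% |
| 0.2 | 0.13 | 0.61 | 11.3% | 11.5% | 14.1% |
| 0.3 | 0.19 | 0.91 | 19.4% | 20.0% | 25.9% |

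Simulation (20,000 trials per cell) agrees. With 99 enrolled and 187 controls, for example, it gives 5.0%, 7.0%, 14.0% and 25.3%. The all-enrolled test on the same simulated data rejects about 5% at every r, but only because the groups were made equal at enrolment.

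**4. The same result without r.** If completers and non-completers differ by g SD for reasons unrelated to the programme, the completer mean moves by 0.4g. For g = 0.25 the shift is 0.10 SD and rejection is 9–10%. For g = 0.5 the shift is 0.20 SD and rejection is 21–28%.

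**5. Effect on a real benefit.** A true 0.50 SD effect in completers would be estimated at about 0.50 + 0.19 = 0.69 SD at r = 0.3.

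**6. Precision of a complier-average estimate.** With 72 enrolled and three controls each (72:216), the all-enrolled SE is √(1/72 + 1/216) = 0.136 SD. Dividing by 0.6 gives 0.23 SD. The completers comparison (72 × 0.6 ≈ 43, against 129) has SE √(1/43 + 1/129) = 0.18 SD.

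**The case against.** **The control side.** A reader might infer that the controls are wholly unfiltered. They are not: they must have given postnatal sweep data, so some struggling controls drop out too. This narrows the asymmetry but does not remove it, because the sweep is meant for all cohort mothers and answering a questionnaire is not the same as attending at least six sessions. The article also does not say which controls enter the completer analysis or whether matching is redone.

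**The size of r.** Nothing in the article supports a value. Matching on prenatal attachment, PHQ-8 and GAD-7 removes whatever part of the selection those scores explain, and only the remainder counts. At r = 0.1 the inflation is small. The 40% is historical and not tied to the 6-session rule. This objection stands: the error rates are conditional.

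**The postnatal requirement.** Table 1 lists six antenatal and three postnatal contacts, and the first postnatal contact is a home visit. If one-to-one contacts count as sessions, which the definition seems to imply, the postnatal condition is easy to meet and much of completion is settled before birth. But antenatal attendance after the baseline questionnaire is also post-baseline behaviour. On the same reading, a mother with all six antenatal contacts and no postnatal one is a non-completer solely because of what happened after birth.

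**The alternative estimator.** Dividing the all-enrolled difference by the completion share has its own weaknesses. It multiplies residual enrolment confounding by 1/0.6 = 1.67, so a 0.10 SD imbalance becomes 0.17 SD. If non-completers gain 0.25 SD and completers 0.50, it returns (0.6 × 0.50 + 0.4 × 0.25)/0.6 = 0.67. This stands, and is why it should not become the sole replacement.

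**Prominence.** A reader might infer that a significant completer result would override a null all-enrolled result. The article does not say so; it lists the all-enrolled analysis first and separates enrolling from receiving.

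**The unseen analysis plan.** It may add an adjustment for selection. The population, the model and the causal wording are nevertheless already fixed in the article.

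**Conclusion.** The point holds as a mismatch between analysis and claim. A comparison conditioned on post-enrolment attendance in one group only, with matching on antenatal variables and a model holding just child age and area, does not by itself estimate the effect of receiving the programme.

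Its size depends on an unknown. With 60% completing, the spurious shift is about 0.64r SD. At the planned sizes, false-positive rates are about 6–7%, 11–14% and 19–26% at r = 0.1, 0.2 and 0.3.

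Two stronger readings are not supported. One is that the completer test will in fact reject well above 5%: the article gives no r, and none is needed for the labelling problem. The other is that the all-enrolled analysis is unbiased: mothers choose to enrol and the study is not randomised, so that contrast avoids this bias only and stays open to unmeasured confounding at enrolment.

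**What to change.** In the Linear regression analyses section:

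1. State that effectiveness conclusions rest on the matched comparison of all enrolled mothers.
2. Restate the completers comparison as descriptive or supportive, and say that it does not estimate the effect of receiving the treatment.
3. Add, as a sensitivity analysis, a complier-average estimate: the matched all-enrolled difference divided by the proportion receiving the programme, with a bootstrap interval. Report it with receipt defined by the 6-session rule and again as any group session.
4. State its assumptions: enrolling without reaching the threshold has no effect, and there is no unmeasured confounding at enrolment, which the division magnifies by about 1.67 at 60% completion.

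The cost is wording and a few lines of Stata. Outcomes are to be collected from all cohort mothers and the service already records attendance, so no new data are needed. The complier-average interval is wider (SE about 0.23 against 0.18 SD with 72 enrolled at 1:3), and the estimate is too large if partial attendance helps; the lower receipt threshold is there to help show this.
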